Therefore, the primary aim of the proposed study is to investigate the effect of two different kinds of exercise programs, i.e., a 12-week game-based HIIT (GameHIIT) program and a 12-week game-based structured aerobic exercise (GameSAE) program, on the executive function of children with ADHD. The secondary aim is to explore a possible mechanism behind the potential association between exercise intervention and improvements in executive function. The hypothesis of the proposed study is that both GameHIIT and GameSAE programs will significantly improve the executive function of children with ADHD, compared with those in the control group. A secondary hypothesis is that the GameHIIT group may confer additional benefits when compared with the GameSAE group.

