### **Sample Size Calculation**

The sample size is calculated using G\*Power 3.1. To elucidate the differences in the executive function tests with a statistical power of 0.9, a conservative effect size of 0.65 based on a previous systematic review with the average effect size calculated regarding the effect of exercise on executive function in children with ADHD [24], a two-tailed alpha level of 0.05, it is determined that 10 participants per group will provide adequate power to detect statistically significant differences. Assuming a 30% loss in the intervention, we will need to approach about 42 eligible participants to achieve the planned sample.

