### **Study Design**

A three-arm school-based randomized controlled trial (RCT) will be conducted to evaluate the effects of two different kinds of 12-week training programs on the executive function of children with ADHD. The design, conduct, and reporting for the RCT adheres to the guidelines of the Consolidated Standards of Reporting trials (<http://www.consort-statement.org/>) [54]. Participants will be randomly assigned to the GameHIIT group, the GameSAE group, or a non-treatment control group using a random number-producing algorithm (with a 1:1:1 allocation ratio within each school). A stratified random sampling procedure will be conducted that considers gender, IQ, and medication status. Raven's Standard Progressive Matrices (SPM) will be used to measure general intelligence. Equal numbers of boys and girls with similar general intelligence will be included in the three groups. Children taking medication will be equally distributed to the three groups. Participants will not be blinded to treatment allocation because of the intervention nature. To avoid contamination between treatment groups, intervention deliverers will be provided with a list of students in the intervention program. Only those on the list can participate in the intervention. During the 12-week intervention period, participants in the control group will maintain their regular PA levels. For ethical reasons, a cross-over study design will be adopted. That is, participants in the control group will receive either GameHIIT intervention or GameSAE intervention according to their preference after a 12-week formal intervention period. Accordingly, participants in the other two groups will have another 12-week follow up. Therefore, it is expected that all participants in the three groups will benefit from the proposed study. The flow diagram of the study design is shown in **Figure 1**.

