### **Statistical analyses**

Statistical analyses of the primary and secondary outcomes will be conducted with the IBM SPSS Statistic for Windows, Version 20.0 (2010 SPSS Inc., IBM Company Armonk, NY). Intervention effects for the primary and secondary outcomes will be examined by two-way (trial × time) analysis covariance (ANCOVA), including group as a fixed factor, pre-post intervention difference (change) as the dependent variable, and age, attendance, sports skill, and ADHD symptoms as covariates. Effect sizes (ES) will be presented as partial eta squared values ( $\eta^2$ ). Pairwise comparison will be performed (post-hoc) with Bonferroni correction, with ES presented as Cohen's *d*. Correlational analysis will also be conducted to evaluate the relationship between the changes in executive function and the fNIRS measures. All data will be presented as mean ± SD, and significance will be set as  $p < 0.05$  for all data analysis.

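### Bonferroni over all post-hoc pairs spends a third of alpha on a contrast the protocol ranks as secondary; Holm on the two planned control contrasts would be a cheap gain in power

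*Protocol*

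**What the plan says.** The Background section of the protocol ranks its hypotheses. The hypothesis of the study is that "both GameHIIT and GameSAE programs will significantly improve the executive function of children with ADHD, compared with those in the control group". The comparison of the two programmes is placed below it: "A secondary hypothesis is that the GameHIIT group may confer additional benefits when compared with the GameSAE group".

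Study Design sets three arms, "with a 1:1:1 allocation ratio within each school". The control group may start either programme after the 12-week period, so T1 is the last time point with an untreated control.

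Statistical analyses takes the pre-post change as the dependent variable and group as the factor, then says: "Pairwise comparison will be performed (post-hoc) with Bonferroni correction". It sets significance at p < 0.05 "for all data analysis". It names no planned contrasts, no order of testing and no divisor.

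Sample Size Calculation uses "a conservative effect size of 0.65", "with a statistical power of 0.9" and "a two-tailed alpha level of 0.05", and arrives at 10 per group. It mentions no adjustment for several comparisons.

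**The concern.** The hypotheses and the testing rule do not match. Two contrasts carry the study hypothesis and a third is secondary, but the analysis treats all pairs alike and calls them post-hoc. If the correction runs over three pairs, the secondary contrast takes one third of the error allowance, and each primary contrast must reach 0.0167.

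With about 10 completers per arm, power to confirm the stated hypothesis is already scarce. Because that hypothesis says both programmes work, the chance that both contrasts reach significance matters as much as the chance for each one.

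**Working it through.** **Inputs.** From the protocol: three arms at 1:1:1, 10 evaluable per arm, effect size 0.65, two-sided 0.05, and change as the outcome. Assumed: 0.65 is Cohen's d (the metric is not stated), the effect is the same in both programmes, and the pre-post correlation is r (none is given; range shown).

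**The plan's own figure.** The stated inputs alone do not reproduce 10 per group. A two-group t-test with d = 0.65 at two-sided 0.05 needs 51 per group for 90% power, and 10 per group gives 28%. If 0.65 is instead Cohen's f for a one-way three-group ANOVA, 34 in total are needed, and 30 give 86%. That is a separate matter. The ordering of the testing rules below holds for any sample size and effect.

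**Thresholds.** Three arms give 3 × 2 / 2 = 3 pairs.
- Bonferroni over three pairs: each contrast at 0.05/3 = 0.0167.
- Holm over the two control contrasts: smaller p-value at 0.05/2 = 0.025; if that is significant, the other at 0.05.

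Both Holm thresholds exceed 0.0167, so every primary rejection under Bonferroni-3 is also a rejection under Holm-2.

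**Effect on the change-score scale.** The SD of a change score is SD × √(2(1 − r)), so d_change = 0.65/√(2(1 − r)):
- r = 0.5: 0.65/1 = 0.65 (no credit for correlation)
- r = 0.7: 0.65/√0.6 = 0.839
- r = 0.8: 0.65/√0.4 = 1.028

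**Single-contrast check.** Noncentrality = d × √(n/2) = 0.65 × √5 = 1.453, with 3 × 10 − 3 = 27 error df. Noncentral t gives power 0.155 at 0.0167, 0.197 at 0.025 and 0.289 at 0.05.

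**Simulated power** (three arms, 10 per arm, pooled variance, 1,000,000 trials per row, both programmes effective):

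| Scenario | Per contrast, Bonferroni-3 → Holm-2 | Both contrasts, Bonferroni-3 → Holm-2 | Per contrast, Holm over three pairs |
|---|---|---|---|
| d = 0.65 | 15% → 22% | 7% → 14% | 17% |
| r = 0.7 (0.839) | 27% → 37% | 14% → 27% | 29% |
| r = 0.8 (1.028) | 41% → 53% | 26% → 43% | 44% |

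Losing 4 df to the four listed covariates hardly changes the first row (15.2% → 21.9% per contrast; 6.5% → 14.0% for both).

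**Familywise error under the global null.**
- Two primary contrasts: Bonferroni-3 0.031; Holm-2 0.046.
- All three contrasts: Bonferroni-3 0.043; Holm-2 with the third tested only after both primaries succeed 0.046; Holm-2 with the third tested ungated at 0.05, 0.083.
- With the gate, the worst value in the partial-null cases tried was about 0.050.

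**Cost to the secondary contrast.** If only GameHIIT works, at 0.65 SD, power for GameHIIT versus GameSAE is 15% under Bonferroni-3 and about 0.2% when gated behind both primaries.

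**The case against.** The strongest reply is that nothing here is wrong. Bonferroni over all pairs is a prespecified, valid and conservative rule that protects every pairwise claim. A trial may choose to protect GameHIIT versus GameSAE, which the protocol does state as a hypothesis. That stands: this is a point of efficiency. Detail on multiplicity may also sit in a statistical analysis plan that is not at hand. But the protocol has already fixed a method, and that method does not follow the protocol's own ranking.

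A reader might infer that Holm on two contrasts gives the extra power at the same error rate, with nothing lost in error control. The figures do not support this. Primary-pair error rises from 0.031 to 0.046, still within 5%, so part of the gain is alpha that the current rule leaves unused. Most of the gain comes from removing the third contrast from the family. Holm over all three pairs adds only about 1 to 3 points per contrast.

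A reader might also quote larger powers from a baseline-adjusted analysis. The protocol models change and does not list baseline executive function among its covariates, so the change-score figures are the relevant ones.

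Finally, the 0.0167 level is inferred. It is the natural reading of unrestricted pairwise comparison in three arms, but the protocol does not write it.

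**Conclusion.** The point holds as a cheap improvement. The testing rule ignores the protocol's ranking and, on its natural reading, gives a third of alpha to the secondary contrast. At 10 per arm, Holm on the two control contrasts adds about 7 to 12 points of power per contrast and about 8 to 17 points for confirming both, with primary-family error at or below 5%. These sizes rest on 0.65 being Cohen's d, equal effects in both programmes and assumed correlations up to 0.8. That Holm-2 never rejects fewer primary contrasts needs none of these assumptions.

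The change does not rescue the design. If 0.65 is Cohen's d, power per contrast after it is 22% to 53% across the range shown, against the planned 90%. Nor does it address multiplicity across the two executive function tests, each with reaction time and accuracy.

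**What to change.** In Statistical analyses, name GameHIIT versus control and GameSAE versus control at T1 as the two planned primary contrasts, tested with Holm at overall two-sided 0.05. Then state one of two rules for GameHIIT versus GameSAE:
- test it at 0.05 only if both primary contrasts are significant, which keeps error over all three at about 5%; or
- report it with its 95% CI as secondary, stating that it has no familywise protection.

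Report adjusted mean differences with 95% CIs for all three contrasts. If the sponsor wants all three protected equally, say so, write the divisor and use Holm over the three pairs, which still uniformly beats Bonferroni.

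The edit is a few sentences and needs no extra participants. The real cost falls on the secondary contrast. Ungated at 0.05, it takes error over all three to about 0.083 under the global null. Gated, it has almost no power when only GameHIIT works. The sponsor should accept that cost knowingly and fix the choice before outcome data are seen.

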Attention-deficit/hyperactivity disorder (ADHD) is a commonly diagnosed developmental disorder, with a 5.3% worldwide prevalence in children and adolescents [18]. The most common symptoms include inattention, impulsivity, impaired inhibition, and hyperactivity [19]. Also, young people with ADHD are often characterized by dysfunction in high level cognitive functions such as executive function [20]. This executive dysfunction may play an important role in the commonly observed behavioral problems in children with ADHD. There are a number of ways to treat ADHD, e.g., medication, psychotherapy, psychoeducation, neuro-feedback, behavior management, etc. Of these treatments, PA and exercise have emerged as effective strategies to manage ADHD given that neither are associated with negative side effects (see recent reviews [21-24]). To summarize, although not always consistently, PA, especially moderate- to high-intensity aerobic exercise, may improve the emotion/mood, behavior, executive function, and some physical measures of children with ADHD. Acute aerobic exercise may have a positive effect on a variety of measures with a large effect size up to 1.26 in children with ADHD [23]. Two studies have reported medium-to-large effects of acute exercise on executive function [25, 26]. Long-term exercise interventions have also been shown to benefit children with ADHD, with improvements in some measures showing a large effect size up to 0.96 [23]. However, these benefits have been mainly described as an improvement of behavioral and emotional problems [22]. Several studies have reported that long-term ‘mixed exercise programs’ may have moderate to significant effects on several aspects of executive function (e.g., inhibition) and attention in children and adolescent with ADHD [27-29], but other studies did not report the same findings [30]. Therefore, so far evidence-based suggestions regarding the optimal exercise for children with ADHD remain somewhat inconsistent [22].

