It is also important to understand the mechanism behind the effect of exercise on the executive function of children. A number of mechanisms have already been proposed to link exercise to executive performance in children with ADHD, including brain structure and activity, neurotransmitter and neurotrophins (such as norepinephrine, dopamine, serotonin, and brain-derived neurotrophic factor), neuroendocrinology, angiogenesis, and cerebral blood flow (see review [3, 48]). It is still unclear what the exact mechanism is behind the exercise benefits, and more studies are required to explore all these possible mechanisms. In the human brain, both the frontal and subcortical regions are believed to be responsible for executive function [4]. However, it is suggested that the prefrontal cortex plays a key role in executive function [49]. Although one previous study suggested that there is improved brain activity in the prefrontal cortex in adolescent with ADHD after aerobic exercise using fMRI technology [28], related studies are quite limited. As mentioned, cerebral perfusion to the prefrontal cortex may be an important mechanism linking exercise to improved executive function, as blood flow will directly influence oxygen delivery [50]. Functional near-infrared spectroscopy (fNIRS) is a sensitive non-invasive means of estimating cerebral hemodynamic response to cognitive tasks by measuring changing levels of oxyhemoglobin (O2Hb), deoxyhemoglobin (dHb), and total hemoglobin (tHb) in the superficial layers of the cortex [51]. The fNIRS has previously been used to investigate real-time changes in cortical oxygenation following an acute bout of exercise and the results show that prefrontal oxygenation is either maintained or increased between moderate and heavy exercise intensities, but may decrease at near-extreme exercise intensities [52, 53]. However, it is not clear whether changes in executive function following a long-term exercise intervention are in fact accompanied by the changes in the cerebral hemodynamic response in the prefrontal cortex, especially for children with ADHD.

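### The planned correlation between executive-function change and the fNIRS measures names no group term, so run across the three arms it cannot separate a within-child association from parallel group shifts

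*Protocol*

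**What the plan says.** The Protocol's background section sets the aim: "The secondary aim is to explore a possible mechanism behind the potential association between exercise intervention and improvements in executive function". Earlier in the same section the open question is put as "whether changes in executive function following a long-term exercise intervention are in fact accompanied by the changes in the cerebral hemodynamic response".

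The only analysis that links the two measures is one sentence under Statistical analyses: "Correlational analysis will also be conducted to evaluate the relationship between the changes in executive function and the fNIRS measures". It names no coefficient, visit, group term or covariates. The ANCOVA for intervention effects in the same paragraph is specified more closely, "including group as a fixed factor, pre-post intervention difference (change) as the dependent variable", with four covariates. The paragraph ends by applying one 0.05 significance threshold to every analysis, so the correlation would be judged by it too.

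The main hypothesis is that "both GameHIIT and GameSAE programs will significantly improve the executive function of children with ADHD" compared with control. The secondary hypothesis allows GameHIIT to do better than GameSAE.

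**The concern.** The trial is designed to create differences between arms in executive function, and the proposed mechanism supposes that exercise also changes the prefrontal response. If both happen, exercised children tend to lie at one end of both scales and controls at the other. A correlation over all children then differs from zero even if, within every arm, those whose fNIRS response changed more improved no more than the rest.

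Group shifts in each measure are already tested by the ANCOVA of each outcome. What a correlation can add is the within-arm association, and a correlation across arms blurs exactly that. The distortion grows with the treatment effect and its false-positive rate grows with sample size. At stake is the reading of the secondary aim; the primary comparison is not affected.

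**Working it through.** The Protocol gives no figure for the correlation, so there is none to reproduce.

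**Inputs**
- Three arms, 1:1:1 (Study Design).
- N = 30, from 10 per group times 3; N = 42 if no recruited child is lost (Sample Size Calculation).
- Two-sided alpha of 0.05.
- Shift on executive function, d = 0.65: "a conservative effect size of 0.65 based on a previous systematic review". The metric is not stated; it is read here as a standardised mean difference.
- Larger values from the background section: 0.96 for long-term exercise ("improvements in some measures showing a large effect size up to 0.96") and 1.26 for acute exercise ("with a large effect size up to 1.26 in children with ADHD").
- Shift on fNIRS: not in the documents. It is assumed, from none up to the same d as executive function.
- True within-arm correlation: zero, with within-arm SD 1 on both measures.

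**Expected correlation across arms.** One third of children have mean 0 and two thirds have mean d. The variance between arms is (1/3)(2/3)d² = (2/9)d² for each measure, and with equal shifts the covariance is the same. So |r| = (2/9)d² / (1 + (2/9)d²).
- d = 0.65: (2/9)(0.4225) = 0.0939; 0.0939/1.0939 = 0.086.
- d = 0.96: (2/9)(0.9216) = 0.2048; 0.2048/1.2048 = 0.170.
- d = 1.26: (2/9)(1.5876) = 0.3528; 0.3528/1.3528 = 0.261.

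With unequal shifts, |r| = (2/9)d₁d₂ / √[(1 + (2/9)d₁²)(1 + (2/9)d₂²)]. This is 0 if either shift is 0.

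**False-positive rate.** The table gives the share of 40,000 simulated trials per row in which the unadjusted Pearson test is significant.

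| Shifts on the two measures | Expected abs(r) | N = 30 | N = 42 |
|---|---|---|---|
| 0 and 0.65 | 0 | 5.1% | 4.9% |
| 0.65 and 0.65 | 0.086 | 7.4% | 8.5% |
| 0.65 and 0.96 | 0.121 | 9.6% | 11.8% |
| 0.96 and 0.96 | 0.170 | 15.0% | 19.1% |
| 0.65 and 1.26 | 0.150 | 12.6% | 15.5% |
| 1.26 and 1.26 | 0.261 | 29.9% | 40.3% |
| Both graded 0 / 0.65 / 1.3 over arms | 0.22 | 21.9% | 29.7% |

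A separate run of 20,000 trials at d = 0.65 and N = 30 gave 7.5%. The graded row illustrates the secondary hypothesis that GameHIIT adds benefit.

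**After removing group.** With each arm centred on its own mean and N − 4 degrees of freedom, the mean correlation is 0.00 and the rate is 4.8% to 5.2% in every row, at both sample sizes.

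**Sign.** The Primary Outcome section records reaction time and accuracy. Improvement lowers the first and raises the second, so the induced correlation may have either sign.

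**The case against.** The strongest reply is that the Protocol never says the correlation is pooled or unadjusted. Within-arm and partial correlations also fit the sentence, and an analysis plan that is not shown may settle it. A reader might infer that the Protocol commits to ignoring group; the text does not support that, because it is silent. What stands against the Protocol is narrower: the paragraph spells out a group factor and covariates for one analysis and none for the next, so an analyst following it as written would run a plain correlation across arms.

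A reader might also infer that a false claim of mechanism is built in, or that a 30% error rate is to be expected. Neither follows. The aim is exploratory, the question is whether the changes accompany each other, and no mediation or causal conclusion is prespecified. The 30% needs a shift of 1.26 on both measures, and that value is an upper figure for acute exercise, whereas this trial runs for 12 weeks. The 0.96 is an upper figure for some measures only, and the background section says that long-term benefits were mainly behavioural and emotional. The background section also says it is unclear whether the hemodynamic response changes at all. At 0.65 the inflation is modest.

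Finally, the sentence may mean fNIRS levels rather than changes. Post-intervention levels that exercise had shifted would be open to the same problem.

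**Conclusion.** The point holds as a minor improvement to the analysis. As written, the correlation has no group term, and run across the arms it cannot tell a within-child association from two parallel group effects. Under equal shifts on both measures and no within-arm association, the expected absolute correlation is about 0.09 to 0.26 and the false-positive rate about 7.5% to 30% at N = 30, over d = 0.65 to 1.26. With no fNIRS shift there is no inflation. The result rests on the assumed fNIRS shift, on reading 0.65 as a standardised mean difference, and on the arms being pooled without adjustment.

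**What to change.** Replace the sentence with a partial correlation, or a regression of executive-function change on fNIRS change, adjusted for randomised group. Use T0 to T1 changes and report a 95% confidence interval. Naming the visits matters because, under Study Design, controls receive one of the programmes after the first 12 weeks, so changes to T2 no longer contrast exercise with no exercise. Adjustment for the T0 values is optional; adjusting for group alone restores the 5% rate.

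The cost is one sentence and two degrees of freedom (28 to 26 at N = 30). Significant results will also be fewer: with a true within-arm correlation of 0.4 and shifts of 0.65, the simulated rejection rate at N = 30 is 58% adjusted against 74% unadjusted. Much of that gap is the group shift, which raises the mean unadjusted correlation to 0.45 against 0.39 adjusted. The adjusted association is still observational within arms and would not by itself establish a mechanism.
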